#### Neuroimaging Data

We will explore changes in phoneme and viseme processing separately and their integration, as a function of the hearing aid use by modeling combinations of MAT, MIS, NOS, and CON, in addition to any change in the functional connectivity using the generalized psychophysiological analytic approach [63]. In addition, we will explore the altered whole-brain connectivity and internetwork coupling using the resting state data. Finally, we will assess the white matter alteration using the VBM approach described above for the gray matter. Furthermore, we will plan to explore changes in the white matter integrity using diffusion tensor analyses and diffusion tractography.

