##### Magnetic Resonance Imaging Assessments

###### Speech Processing Task

During fMRI scanning, participants will view a series of human faces (1 male and 1 female actor) that mouth words in blocks (or “epochs”) lasting 16 seconds (1 word per 2 seconds) each. Each block will be one of 4 conditions termed *matched* (MAT), *mismatched* (MIS), *no sound* (NOS), and *control* (CON), preceded and followed by 10-second rest periods, where a fixation cross (“+”) will be displayed. In each of 2 scanning runs, 4 repetitions of each block type (16 total blocks per run) will be presented in a pseudorandom order, each utilizing different word stimuli. The stimulus presentation time for each of the two scanning runs will be 426 seconds (7 minutes 6 seconds); an additional 20 seconds of imaging data will be acquired following the end of the stimulus presentation to allow the hemodynamic response to return to the baseline.

During MAT, the faces will mouth single syllable, high-frequency words (visual stimuli), such as “cat” or “house,” and the corresponding audio input (auditory stimuli) will be played through the headphones. During MIS, the stimuli will remain the same, but the mouthed words and auditory stimuli will be semantically unrelated (eg, “cat” is mouthed but “house” is heard). During NOS, the visual stimuli will be presented but not the auditory stimuli. During CON, the faces will be presented but will not mouth the words; instead, they will simply open and close the mouth without auditory stimuli. All participants will be asked to press a button whenever a face appears to ensure participant attendance to the task.

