##### Speech Processing Task Data: Functional Alteration

First, we will compute the contrast of MAT>NOS (NOS controls for viseme processing) for each participant and enter the contrasts into an RMMM to assess the effect of the first-time hearing aid use on speech sound processing; (2) we will assess changes in the functional connectivity in key areas determined from this analysis using the generalized psychophysiological analytic approach [63]; (3) finally, we will use key areas of difference as seeds in the functional connectivity analysis of the resting state data.

Secondly, we will compute the contrast of NOS>CON (CON controls for basic face motion processing) for each participant and enter the contrasts into an RMMM to assess the effect of the hearing aid use on viseme processing; (2) we will assess changes in the functional connectivity in key areas determined from this analysis using the generalized psychophysiological analytic approach [63]; (3) finally, we will use key areas of difference as seeds in the functional connectivity analysis of the resting state data.

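### The primary MAT>NOS contrast measures speech sound plus any congruent audiovisual response, and the planned split of phoneme processing from integration needs an assumption the protocol does not state

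*Protocol article*

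**What the plan says.** The section Speech Processing Task defines the design: "Each block will be one of 4 conditions termed *matched* (MAT), *mismatched* (MIS), *no sound* (NOS), and *control* (CON"). In MAT a face mouths a word and the same word is heard. In MIS "the stimuli will remain the same, but the mouthed words and auditory stimuli will be semantically unrelated". NOS shows the mouthing face in silence, and CON shows a mouth that opens and closes without words or sound.

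Under Primary Statistical Analyses (Speech Processing Task Data: Functional Alteration), the first contrast is MAT>NOS, with NOS described as the control for viseme processing. Its group-by-time model is meant to "assess the effect of the first-time hearing aid use on speech sound processing". The second contrast, NOS>CON, is assigned to viseme processing. MIS enters neither. Regions found with each contrast then feed the psychophysiological connectivity analysis and serve as resting-state seeds.

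Under Exploratory Analyses (Neuroimaging Data), the article adds: "We will explore changes in phoneme and viseme processing separately and their integration, as a function of the hearing aid use", by modelling combinations of the same four conditions.

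**The concern.** No block presents speech sound without visible mouthing of a word. Subtracting NOS from MAT removes the face and the viseme response, but it leaves whatever the brain does when seen and heard speech coincide. A change in that audiovisual response would be reported as a change in speech sound processing.

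This alternative is not remote. The Introduction says that people with SNHL come to rely more on visual cues, and it links functional alteration to weakened associations between phonological and viseme processes as the loss progresses. The section on scan acquisition itself refers to the paradigm as a sensory integration task. At stake is the mechanism attached to the first primary imaging result, and the meaning of the connectivity analyses seeded from it.

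**Working it through.** **1. Is there a fifth block type that the text does not describe?** Inputs, all from Speech Processing Task: "4 repetitions of each block type (16 total blocks per run"); "mouth words in blocks (or “epochs”) lasting 16 seconds (1 word per 2 seconds) each"; each block "preceded and followed by 10-second rest periods"; and "The stimulus presentation time for each of the two scanning runs will be 426 seconds (7 minutes 6 seconds").

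- Rests shared between neighbouring blocks: 16 × 16 s + 17 × 10 s = 256 + 170 = 426 s. This is the stated figure exactly.
- Separate rests before and after each block: 16 × 16 s + 32 × 10 s = 576 s. This does not match.

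The run time is fully accounted for by the four named conditions, so no sound-only block is hidden in it.

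**2. What each condition contains.** I extend the protocol's own subtraction logic with an additive model. Let F = face motion, V = viseme, A = speech sound, Ic = congruent audiovisual response, Im = response to audiovisual mismatch.

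| Condition | Content |
|---|---|
| MAT | F + V + A + Ic |
| MIS | F + V + A + Im |
| NOS | F + V |
| CON | F |

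**3. What the contrasts estimate.**

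| Contrast | Quantity |
|---|---|
| NOS − CON | V |
| MAT − NOS | A + Ic |
| MIS − NOS | A + Im |
| MAT − MIS | Ic − Im |

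Viseme processing is separable. With all five terms kept, the design matrix has rank 4, and A, Ic and Im are not individually estimable. That rank alone proves little, since four conditions can never identify five free terms. The real question is whether Im may be dropped.

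**4. With Im = 0.** The model has four terms and rank 4, so every term is estimable: A = MIS − NOS and Ic = MAT − MIS. MAT − NOS is still A + Ic. For group-by-time effects, it is enough that Im does not change differently between the groups.

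**5. Illustration with arbitrary unit changes** (not estimates for this trial):

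| Change in A, Ic, Im | MAT − NOS | MIS − NOS | MAT − MIS |
|---|---|---|---|
| 1, 0, 0 (sound only) | 1 | 1 | 0 |
| 0, 1, 1 (both audiovisual terms) | 1 | 1 | 0 |
| 0, 1, 0 (congruent term only) | 1 | 0 | 1 |

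All three rows give the same MAT − NOS. MIS distinguishes the third from the first, but no contrast distinguishes the first from the second unless Im is fixed by assumption.

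**The case against.** The strongest reply is that the limit depends on a model the protocol never wrote down. With four components instead of five, the design is full rank and the exploratory section can deliver what it promises. That section is labelled exploratory, fixes no contrast, and names MIS among the conditions to be combined, so MIS>NOS and MAT versus MIS are already within reach. Its wording can also be read as separating phoneme from viseme processing, with MAT versus MIS as an index of integration. Finally, the study hypothesis concerns altered activation of the auditory cortices and attendant networks, and altered connectivity. Testing it does not require separating sound from integration.

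Much of this stands. A reader might infer that no combination of the four conditions can isolate sound or integration. The documents do not support so flat a statement, because step 4 shows that both are estimable if the mismatch response is zero. A reader might also infer that the protocol predicts a hearing-aid effect on audiovisual matching. It does not: the weakened phonological-viseme association is tied to progression of SNHL, while the statements on hearing aids concern preserving auditory function and protecting auditory areas.

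Two things survive. The assumption that makes the split possible is not stated anywhere. And the label on the primary contrast is too narrow even when that assumption is granted.

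**Conclusion.** The point holds as one of interpretation and labelling, with its main weight on the primary analysis. MAT>NOS estimates speech sound plus any congruent audiovisual response, whatever is assumed about MIS. The exploratory separation of phoneme processing from integration is valid only if mismatched audiovisual speech evokes no interaction or conflict response, or none that changes differentially. Viseme processing is separable by the protocol's own subtraction.

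The size of the possible misattribution cannot be given, because the article contains nothing from which to estimate an integration response. The algebra assumes additive components, as the protocol's subtractions do.

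The group-by-time test of altered auditory-cortex activation is unaffected. It is also tempting to conclude that matching changes in MAT>NOS and MIS>NOS would establish a speech-sound change. They would not: the second row of the illustration moves both contrasts with no change in sound.

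**What to change.** In Speech Processing Task Data: Functional Alteration:

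- Describe MAT>NOS as the response to speech sound in an audiovisual context.
- Report the MIS>NOS group-by-time model and a direct MAT − MIS group-by-time test beside it.
- Interpret MAT − MIS as a congruency effect. Do not infer congruency from MAT>NOS being significant while MIS>NOS is not, since that pattern is not a test of their difference.

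In the exploratory Neuroimaging Data section:

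- Replace the promise of separate phoneme processing and integration with the estimable quantities: sound in an audiovisual context, viseme, and congruent versus incongruent speech.
- State that sound and integration are separable only if the mismatch response is assumed to be zero or unchanged.

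The cost is one or two extra models on data the task already yields, and a narrower stated conclusion. The task and the scanning do not change. A sound-only condition would remove the need for the assumption, but at the present block and rest lengths it would lengthen each run to 20 × 16 + 21 × 10 = 530 s, which is 104 s more than the current 426 s. It is not needed for this correction.

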## Results

The speech processing task was programmed and tested during September 2017-December 2017. Training of research staff on research protocols (cognitive, hearing, and MRI session testing) was conducted intermittently between February 2016 and February 2020. In addition, the baseline testing sessions will commence in February 2018 and will be completed by June 2020, and the follow-up sessions will be completed by December 2020. Furthermore, baseline session data analyses will be completed by October 2019, and final longitudinal data analyses will be completed by July 2020.

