**Results:**

This research is funded by the Barbara Dicker Brain Sciences Foundation Grants, the Australian Research Council, Alison Hennessy Audiology, and Chelsea Hearing Pty Ltd under the Industry Transformation Training Centre Scheme (ARC Project #IC140100023). We obtained the ethics approval on November 18, 2017 (Swinburne University Human Research Ethics Committee protocol number SHR Project 2017/266). The recruitment began in December 2017 and will be completed by December 2020.

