## Methods

### Study Design

The study is a prospective cohort design evaluating the effect of the hearing aid use on cognition, psychosocial factors (eg, depression and social interaction), and neural function. We will recruit 2 participant groups of similar size consisting of people with mild to moderate SNHL. Of note, group randomization is not possible in this study; however, the groups will be matched as much as possible in terms of the degree of hearing loss.

Group A: Patients with SNHL who have used hearing aids for, at least, the previous 12 months and plan to continue using their hearing aids for the next 6 months.Group B: Patients with SNHL who have never used hearing aids before and who will be willing to wear hearing aids for the next 6 months.

All participants would be asked to complete, at 2 time points (t) including baseline (t=0) and follow-up (t=6 months), tests of hearing and psychosocial and cognitive function and attend an MRI session.

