### Study Power Analysis

With 30 consented participants in each group with a significance level of 5%, the power of 80%, and controlling for age, gender, and level of education, the baseline analysis of covariance (ANCOVA) model for spatial working memory performance can detect effect sizes of *d*=0.63 for between-group differences. Allowing 10% attrition in the 6-month follow-up period, a sample size of 27 in each group with a significance level of 5% and power of 80%, a significant group-by-time interaction effect can be detected for a large effect size of *d*=0.77. This study is based on the assumption that an effect size of *d*

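### The stated timeline contradicts itself: both analysis deadlines fall before the matching data collection ends, and the abstract's recruitment end date fits neither the baseline window nor a 6-month follow-up

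*Protocol article*

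**What the plan says.** The Results section of the protocol article gives four dates:

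- Baseline collection: "the baseline testing sessions will commence in February 2018 and will be completed by June 2020".
- Follow-up collection: "the follow-up sessions will be completed by December 2020".
- Baseline analysis: "baseline session data analyses will be completed by October 2019".
- Longitudinal analysis: "final longitudinal data analyses will be completed by July 2020".

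The Results paragraph of the abstract adds a fifth: "The recruitment began in December 2017 and will be completed by December 2020".

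Two other sections bear on these dates. Study Design has every participant assessed "at 2 time points (t) including baseline (t=0) and follow-up (t=6 months"). Study Power Analysis takes 30 per group at baseline and, for the group-by-time interaction, says "Allowing 10% attrition in the 6-month follow-up period, a sample size of 27 in each group", with a detectable effect of d=0.77 at 80% power. The article describes no interim or partial-data analysis.

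**The concern.** An analysis called final has a completion date earlier than the date by which its data will exist, and so does the baseline analysis. A reader cannot tell which participants either analysis is meant to include. The recruitment date in the abstract adds a second conflict: a person recruited after June 2020 has no baseline slot in the stated window and cannot have a 6-month visit by December 2020.

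At stake is the link between the schedule and the stated power. The interaction test is sized on 27 per group with follow-up. If the July 2020 date were kept while baseline testing ran to June 2020, the latest enrolled participants would have no 6-month data in that analysis, and the planned number could not be relied on.

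**Working it through.** **Inputs.** Baseline testing February 2018 to June 2020, follow-up end December 2020, baseline analysis October 2019, final analysis July 2020 (all Results section). Recruitment end December 2020 (abstract). Follow-up length 6 months (Study Design). 30 per group at baseline and 27 per group at follow-up (Study Power Analysis).

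**1. Do the collection dates agree with each other?** June 2020 + 6 months = December 2020. Yes: the stated follow-up end is reproduced from the stated baseline end.

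**2. Do the analysis dates fit them?**

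| Analysis | Analysis completed by | Data collection completed by | Gap |
|---|---|---|---|
| Baseline | October 2019 | June 2020 | 8 months |
| Final longitudinal | July 2020 | December 2020 | 5 months |

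July 2020 is 1 month after the last baseline session. July 2020 − 6 months = January 2020, so nobody with a baseline after January 2020 can have a 6-month visit by then.

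**3. Does the abstract fit?** Recruitment to December 2020 runs 6 months past the end of baseline testing. December 2020 + 6 months = June 2021, which is 6 months after the stated follow-up end and 11 months after the stated final analysis.

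**4. Illustration of size, if the dates were followed literally.** The article gives no accrual curve, so I assume that 60 participants accrue evenly from 1 February 2018 to 30 June 2020 (880 days).

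- Baselines by 31 October 2019: 60 × 637/880 = 43.4.
- Baselines by 31 January 2020, hence 6-month visits due by 31 July 2020: 60 × 729/880 = 49.7.
- Per group after 10% attrition: 49.7/2 × 0.9 = 22.4, taken as 22.

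Power uses a two-sided two-sample t test at 5% with n per group: noncentrality d × √(n/2), degrees of freedom 2n − 2.

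| n per group | Detectable d at 80% power | Power at d=0.77 |
|---|---|---|
| 27 (planned) | 0.777 | 79.3% |
| 22.5 | 0.85 | 71% |
| 22 | 0.865 | 70.4% |

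The first row reproduces the article's d=0.77 to within rounding, so the method is a fair basis for comparison. Rounding 22.4 down to 22 matters little.

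**5. Range.** The result depends on the share of 6-month visits done by July 2020, with n = 27 × share. The shares other than 83% are assumed.

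| Share | n per group | Detectable d | Power at d=0.77 |
|---|---|---|---|
| 75% (late-loaded accrual) | 20.2 | 0.90 | 67% |
| 83% (even accrual) | 22.4 | 0.86 | 71% |
| 90% | 24.3 | 0.82 | 75% |
| 100% (collection finished early) | 27 | 0.78 | 79% |

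**The case against.** **The completion dates are only latest dates.** Collection could finish early, and then nothing is lost. This stands as a limit on the size of the effect, but it does not remove the conflict. For both analyses to be complete on their stated dates, baseline testing would have to end by October 2019 and follow-up by July 2020. The June and December 2020 dates would then need correcting instead.

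**It may be a clerical slip.** This is plausible. The same paragraph reports staff training in the past tense up to February 2020 while placing the start of baseline testing in February 2018 in the future, which looks like a partly updated timeline. A reader might infer from the dates that the investigators plan to analyse incomplete data, or that staff will know results while testing is still open. The article does not say so, and unrevised dates explain the text at least as well.

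**Type I error.** A reader might also infer an unplanned extra look. If the longitudinal test were run at about 83% of the data and again at the end, each at 5%, and either result were claimed, the error would be about 6.9% (correlation of the two statistics √0.83). That is hypothetical. The article describes no second longitudinal test, and if only the complete-data test is used for inference its error stays at 5%. The argument does not reach the October 2019 analysis at all, since the baseline ANCOVA tests a different question from the group-by-time interaction. The power loss (no rerun) and the inflated error (rerun) are alternatives and must not be added together.

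**The mixed model accommodates missing data.** This is true of the non-imaging outcomes, so late participants could still contribute a baseline value. With two time points, a baseline value alone carries little information on change. The whole-brain fMRI analyses take only participants who complete the protocol.

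**Conclusion.** The point holds as an internal inconsistency in the stated schedule. The gaps of 8 and 5 months, and the misfit of the abstract's recruitment date, are exact and rest on no assumption; no other section resolves them.

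The consequence is conditional. It arises only if July 2020 is kept while baseline testing runs past January 2020. Its size also depends on accrual: at even accrual, about 22 per group instead of 27, a detectable d of about 0.86 instead of 0.77, and power of about 70% instead of 79%. Early completion of collection shrinks this loss to nothing. The documents do not support the stronger conclusions that an analysis on incomplete data is planned or that the type I error is inflated.

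**What to change.** Reconcile the dates in the abstract and the Results section so that:

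- recruitment ends no later than baseline testing;
- the final longitudinal analysis is dated after the last 6-month follow-up session;
- the baseline analysis is dated after the last baseline session or, if an earlier report is wanted, is labelled preliminary.

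The investigators need to say which dates are current. If the June and December 2020 collection dates are kept, the final analysis moves from July 2020 to after December 2020. If the analysis dates are kept, baseline testing must close by October 2019 for a complete baseline analysis. For the final analysis, the last baseline would be January 2020.

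The change is to dates only and needs no new participants or procedures. If the collection dates stand, the cost is later reporting, by at least five months for the longitudinal results.

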## Discussion

### Summary

SNHL is strongly associated with cognitive decline, social and mental health problems, and incident dementia. SNHL leads to brain atrophy and neuroplasticity that may be detrimental to auditory rehabilitation. Some evidence indicates that the use of hearing aids may slow or improve this pathology. In this retrospective cohort study, we utilize cognition and psychosocial testing in combination with structural and functional neuroimaging to assess the impact of the hearing aid use on the neurocognitive function and brain structure in those with SNHL. To the best of our knowledge, this is the first study to directly assess structural and functional brain changes arising from the use of hearing aids in older adults with SNHL. Currently, there is a paucity of neuroimaging studies in the SNHL field generally, which is surprising given what is known about neural plasticity in SNHL. A chief motivation for this work is to address this shortcoming, yielding critical data for SNHL research and ideally, may prompt greater use of hearing aids in those with SNHL.

### Limitations

This study has some limitations that must be addressed. There are numerous aspects of speech processing, in general, and its impairment in SNHL. In this study, we have chosen to examine the processing of one aspect alone, namely monosyllabic word processing. This approach was selected to make the task easy to perform for participants and to ease data interpretation. Hence, our analyses will not reveal all aspects of speech processing dysfunction in SNHL such as sentence comprehension [64]. In addition, studies examining the cognitive impairment in SNHL have not utilized consistent neuropsychological testing protocols; hence, the component processes probed across studies might not be consistent, inhibiting the generalization of findings across studies. However, here we use a standardized battery that has been found to be particularly sensitive in older adults [52].

